**Table 1 Hamstring and Quadriceps Muscle Strength Outcomes at 4, 8, and 12 Weeks, Mean  $\pm$  SD**

| Muscle                         | Limb       | Time Point       |                  |                  | P     |
|--------------------------------|------------|------------------|------------------|------------------|-------|
|                                |            | 4 wk             | 8 wk             | 12 wk            |       |
| Hamstring peak torque (Nm/kg)  | Involved   | 1.0 $\pm$ 0.5*   | 1.32 $\pm$ 0.9*  | 1.55 $\pm$ 0.8*  | <.001 |
|                                | Uninvolved | 1.86 $\pm$ 0.34† | 1.89 $\pm$ 0.46  | 2.05 $\pm$ 0.38† | .001  |
| Quadriceps peak torque (Nm/kg) | Involved   | 1.47 $\pm$ 0.62* | 2.18 $\pm$ 0.65* | 2.61 $\pm$ 0.67* | .001  |
|                                | Uninvolved | 2.60 $\pm$ 0.63* | 2.88 $\pm$ 0.73* | 3.14 $\pm$ 0.64* | .001  |

\*Quadriceps and hamstrings peak torques were significantly different between the 4th, 8th, and 12th weeks for the involved limb, and quadriceps peak torque was significantly different between the 4th, 8th, and 12th weeks for the uninvolved limb. †Significant difference for hamstrings peak torque between the 4th and 12th weeks for the uninvolved limb.

**Figure 11:** Sample size for the RCT based on the study by Harput (2015)

## Data Management and Confidentiality

Only the supervisor, Principal Investigator (PI), co-researcher, and independent statistician have the right to access the data, and it will not be disclosed to any non-relevant party. The researcher supervisor and the PI will provide advisory support to the trial investigators in monitoring withdrawals, assessing ethical conduct, addressing missing data and reviewing major adverse events. A case report form (CRF) will record instances of unavailable data, ensuring uniformity and precision, and providing essential information for analysis and management. The data will be stored in a secure cabinet in the office of the PI and will be preserved for at least 5 years after the study is finished and published.

## Statistical Analysis

The data analysis will be conducted using the SPSS Windows Version 29.0 software (SPSS, Chicago, IL, USA). The data will be summarised using descriptive statistics such as the mean and standard deviation, median and interquartile range, quantity and percentage, and frequency, depending on the distribution and type of data. This encompasses participant demographics as well as adherence to exercise. To evaluate the normality of the data, we will examine the skewness and kurtosis statistics (the ratio of the statistic to the standard error) by conducting the Shapiro-Wilk test. Boxplots are employed to detect outliers.

The main outcome measure, the mean changes in hamstring isometric peak force between 4 and 12 weeks, will be assessed using a paired t-test. The main hypothesis will be tested by comparing the changes in the mean difference between the intervention group and the standard

care group. The missing data will be analysed according to the intention-to-treat concept, considering the groups to which participants have been randomly allocated. Descriptive analysis, on the other hand, will describe missing data patterns in great detail to look for possible biases. If the data distribution exhibits non-normality or ceiling/floor effects, a non-parametric test (specifically, the Mann-Whitney test) will be conducted. Furthermore, this study will employ one-way repeated-measures ANOVA within-group measurements to investigate potential differences between the Quadriceps Index and Hamstring Index over an interval of time.

The secondary outcome data, which includes measurements of hamstring flexibility, range of motion, IKDC scores, and exercise adherence, will be summarised and evaluated in a manner consistent with the primary result. A repeated measures analysis of variance (ANOVA) will be used to examine the impact of rehabilitation and time on all the measured variables.

Statistical significance will be determined by a p-value of less than 0.05 (two-tailed) for all conducted tests with a 95% confidence interval.

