## **Research Hypothesis**

We hypothesise that participants receiving the ULIT plus standard care will have better hamstring strength at 12 weeks post-operatively compared to participants receiving a standard care rehabilitation program alone.

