### *Null Hypothesis*

There is no significant difference between the combination of ULIT and standard care rehabilitation compared to the standard care rehabilitation alone on hamstring strength in early phase ACLR.

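### The test named for the primary outcome (a paired t-test) is within-group and does not match the between-group hypothesis; the between-group test is announced but not named.

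*Protocol*

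**What the plan says.** The hypotheses compare the groups. The null reads "There is no significant difference between the combination of ULIT and standard care rehabilitation compared to the standard care rehabilitation alone", and the Research Hypothesis expects that "participants receiving the ULIT plus standard care will have better hamstring strength at 12 weeks post-operatively".

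The Statistical Analysis section then names or implies five analyses:

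- For the primary outcome: "The main outcome measure, the mean changes in hamstring isometric peak force between 4 and 12 weeks, will be assessed using a paired t-test".
- For the main hypothesis: "The main hypothesis will be tested by comparing the changes in the mean difference between the intervention group and the standard" care group. No test is named.
- If the data are non-normal or show ceiling or floor effects: "a non-parametric test (specifically, the Mann-Whitney test) will be conducted".
- For the Quadriceps and Hamstring Indices: "one-way repeated-measures ANOVA within-group measurements".
- At the end of the secondary-outcome paragraph: "A repeated measures analysis of variance (ANOVA) will be used to examine the impact of rehabilitation and time on all the measured variables".

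One significance rule covers them all: "Statistical significance will be determined by a p-value of less than 0.05 (two-tailed) for all conducted tests with a 95% confidence interval".

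**The concern.** A paired t-test takes the same patients at two times and asks whether their mean change is zero. It has no term for treatment group. The two arms are independent, randomised 1:1 and unmatched, so the phrase cannot be read as a paired comparison of ULIT with control.

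Patients in both arms are expected to regain hamstring strength between weeks 4 and 12 whatever ULIT does. A significant paired test in the ULIT arm would therefore mostly report normal post-operative recovery. Because this is the only parametric test explicitly tied to the primary outcome, the analyst could report it and regard the plan as followed. The comparison that answers the question would then be left to a later choice among an unnamed test, a Mann-Whitney test and a repeated-measures ANOVA.

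**Working it through.** **Matching each analysis to the hypothesis**

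| Analysis in Statistical Analysis | Compares | Tests ULIT against standard care? |
|---|---|---|
| Paired t-test, week 4 to week 12 (primary outcome) | Two times, same patients | No |
| Comparison of changes between groups (main hypothesis) | Two groups | Yes, but no test named |
| Mann-Whitney (fallback) | Two independent samples | Yes, but it is not the counterpart of a paired t-test |
| One-way within-group repeated-measures ANOVA (indices) | Times within a group | No |
| Repeated-measures ANOVA, rehabilitation and time (all variables) | Probably group and time | Possibly, through group-by-time, which is not identified as primary |

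Read literally, a failed normality check would change the question (from recovery to a group difference) as well as the method.

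**How often a paired test is significant when ULIT does nothing**

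The plan gives no figure of its own for this, so the inputs are partly assumed:

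- Mean change in both arms: 1.55 − 1.0 = 0.55 Nm/kg, from involved-limb hamstring torque at weeks 4 and 12 in Table 1 (a single cohort in the cited study).
- SD of change: 0.71 as a central assumption. The Sample Size section gives 0.71 for the main outcome measure, which it calls a symmetry index, and does not say that it is the SD of a change.
- Range for the SD of change, from the Table 1 SDs (0.5 and 0.8) and an assumed within-patient correlation r: SD = √(0.5² + 0.8² − 2r × 0.5 × 0.8) = √(0.89 − 0.8r). This gives 0.81 at r = 0.3 and 0.50 at r = 0.8. An SD of 0.71 corresponds to r of about 0.48.
- n per arm: 14 (stated minimum) and 16 (planned); 14/(1 − 0.10) = 15.6, rounded up to 16. Alpha is 0.05, two-sided.

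The probability p that a paired test is significant comes from the noncentral t distribution with n − 1 degrees of freedom and noncentrality (0.55/SD) × √n.

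- n = 14, SD 0.71: noncentrality 0.775 × 3.742 = 2.90, critical value 2.16, p = 0.764.
- n = 16, SD 0.71: noncentrality 0.775 × 4 = 3.10, critical value 2.13, p = 0.825.

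The arms are independent, so the chance of ULIT significant and control not is p(1 − p).

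| SD of change | n per arm | ULIT paired test significant | ULIT significant, control not |
|---|---|---|---|
| 0.81 (r = 0.3) | 14 / 16 | 66% / 72% | 23% / 20% |
| 0.71 | 14 / 16 | 76% / 83% | 18% / 14% |
| 0.50 (r = 0.8) | 14 / 16 | 97% / 98% | 3.2% / 1.6% |

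A simulation of 40,000 trials at SD 0.71 agrees: 76% and 83% for the paired test, 18% and 14% for the split pattern. In the same trials an independent-samples t-test on the changes rejected in 5.0%, as it should.

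**Does covariate adjustment cost precision?**

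For a week-4 covariate with the Table 1 SDs, ANCOVA residual variance is 0.64(1 − r²) and change-score variance is 0.89 − 0.8r. The ratio is 0.90, 0.98, 1.00 and 0.92 at r = 0.3, 0.5, 0.6 and 0.8, so there is no variance penalty and a modest gain at most. The documents give no figure from which to compute the gain from the preoperative value.

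**The case against.** The strongest reply is that the plan's intent is between-group. The sentence after the paired t-test assigns the main hypothesis to a comparison of changes between the arms. The Mann-Whitney fallback is the natural counterpart of an independent-samples test on those changes, and the Sample Size section works from a difference between two means. The rehabilitation-and-time ANOVA covers all variables and most naturally has group as a factor. On this reading one phrase is out of line, and an analysis plan that is not shown might name the test.

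Much of this stands, and it rules out two stronger readings. A reader might infer that no between-group comparison is planned; the text announces one. A reader might also infer that a significant result within the ULIT arm, or one in ULIT but not in control, would count as success; no section adopts either as a decision rule. The split-pattern percentages therefore show what such a reading would cost, and they depend heavily on the assumed SD.

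The reply does not remove the inconsistency. The protocol does not leave the primary test open for a later document. It names one, and that test cannot address the hypothesis.

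A further fair point concerns any remedy that uses week 4. Randomisation and Allocation places allocation straight after preoperative baseline testing, so week-4 strength is post-randomisation. The Intervention Group section starts ULIT in the fourth week, while Data Collection allows ±14 days around the week-4 visit. Some week-4 values may therefore follow the first ULIT session, and adjusting for them could remove part of the effect. A change score from week 4 has the same weakness.

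**Conclusion.** The point holds as an inconsistency between the named primary test, the hypothesis and the fallback, together with a between-group test that is announced but not named. It should be corrected before analysis because it concerns the primary outcome.

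The mismatch follows from the wording alone and needs no numerical assumption. The size of the risk does rest on assumptions: equal recovery of 0.55 Nm/kg in both arms, normally distributed changes, and an SD of change that the protocol does not state. A paired test in the ULIT arm would then be significant in about 66-98% of trials with no ULIT effect (76-83% at SD 0.71), which is high throughout the range. The pattern of ULIT significant and control not would occur in about 2-23% (14-18% at SD 0.71).

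A reader might also infer that preoperative strength goes unused. The documents support only that it is not named as a covariate, since the rehabilitation-and-time ANOVA could include it.

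**What to change.** Replace the paired t-test with one named primary analysis: ANCOVA of operated-limb hamstring strength at 12 weeks, with group as factor and the preoperative (pre-randomisation) value as covariate. This matches the 12-week wording of the Research Hypothesis and uses data already collected. Report the adjusted mean difference, its 95% confidence interval and the two-sided p-value.

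Add week-4 strength as a second covariate only where it is documented as measured before the first ULIT session. Apply the same condition to any change score from week 4.

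If normality fails, use a rank-based or permutation version of the same between-group comparison, so that the question stays the same. Label the paired t-test and the within-group ANOVA as descriptive, and state that the rehabilitation-and-time ANOVA is not the primary test.

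The cost is a few sentences of protocol text and one degree of freedom, or two with the week-4 covariate. The analysis is standard in SPSS.

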## **S1 Appendix. Study Protocol for Ethics Application**

### **EFFECT OF UPPER LIMB ISOMETRIC TRAINING ON HAMSTRING STRENGTH IN EARLY POSTOPERATIVE ANTERIOR CRUCIATE LIGAMENT RECONSTRUCTION PATIENTS: A RANDOMISED CONTROLLED TRIAL**

#### **Abstract**

This study aims to investigate the effects of upper limb isometric training (ULIT) combined with standard care of an anterior cruciate ligament reconstruction (ACLR) rehabilitation program on hamstring strength and physical function in the early-phase postoperative period. Early recovery of hamstring strength is critical for knee stability and functional rehabilitation post-ACL surgery. Hamstring strength deficits are prolonged issues in rehabilitation, with significant hamstring strength deficiencies in an early postoperative ACLR, especially using hamstring autograft, leading to functional limitations and an increased risk of secondary injuries. High knee muscle strength imbalances can hinder strength return in later stages. However, swelling, donor site pain, joint stiffness, and graft protection often neglect the direct activation of the hamstring in the early period. Also, clinical practice guidelines and consensus on early rehabilitation strategies are conflicting. While lower limb strengthening exercises are the mainstay of rehabilitation, this study explores the potential benefits of ULIT in promoting hamstring activation through the inter-limb posterior myofascial kinetic chain. This study hypothesise that participants receiving ULIT in addition to standard care will demonstrate better hamstring strength at 12 weeks post-operatively compared to those receiving standard care rehabilitation alone. A total of 32 patients who underwent ACLR with hamstring tendon autografts will be randomly assigned to either the ULIT group or a control group. The ULIT group performed upper limb isometric exercises in addition to standard postoperative rehabilitation, while the control group followed the standard rehabilitation protocol alone. We will measure hamstring and quadriceps strength using hand-held dynamometry at baseline (preoperative), 4, 8, and 12 weeks postoperatively. The primary outcome is the change in hamstring strength in the operated limb, while secondary outcomes included hamstring flexibility and patient-reported outcomes on symptoms, physical function and adherence. Statistical analysis will be conducted to compare the strength recovery between the two groups. It is believed that the results of this study will enhance knowledge about the global functional muscle concept, offer effective, safe, inexpensive, and feasible interventions, and promote further research on the interlimb connection of muscle activation and flexibility in heterologous muscle groups after ACLR.

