## **Randomisation and Allocation**

Following the baseline assessments, individuals will be assigned either to the intervention group or the control group by a simple random sampling. The randomisation process will be performed using a computer-generated sequence numbering scheme ranging from one (1) to thirty-two (32), with an equal allocation ratio of 1:1. The concealment is achieved using a set of sealed and numbered envelopes. Allocation takes place following baseline testing (T1), when a staff of the Orthopaedic Department, who is not participating in the study, opens the next study envelope. Subsequently, they notify the group assignment to the attending physiotherapist. The envelopes will be securely stored and sealed in a cabinet to ensure security and prevent any unauthorised access. Measures will be implemented to restrict the number of authorised individuals who have access or authority to open the research envelopes, to prevent any potential bias in the allocation process. The statistical analysis will specifically focus on allocation codes, ensuring that the data analyzers remain unaware of the study group allocation (see Figure 9).

[figure not shown]

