## Sample Size

Sample size calculations are performed using SPSS version 29 for the primary outcome: differences between two means of Hamstring MVIC peak force symmetry index (see Figure 11). With the population standard deviation for the main outcome measure amount of 0.71 as in the Harput et al. study, type I error of 0.05, type II error of 0.2, 80% power, the minimum sample size required is 14 patients per group (28 in total). Expecting an attrition rate of 10%, 16 participants are considered for each study group.

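### The primary and secondary between-arm comparisons use unadjusted changes although pre-randomisation values exist for each measure, which probably loses precision; adjust for both pre-operative and week-4 force, and for pre-operative IKDC and AKET

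*Protocol*

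**What the plan says.** The Abstract sets the schedule: "We will measure hamstring and quadriceps strength using hand-held dynamometry at baseline (preoperative), 4, 8, and 12 weeks postoperatively". Under Randomisation and Allocation the order is explicit: "Allocation takes place following baseline testing (T1". The same section describes simple randomisation, 1:1, with no stratification.

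Statistical Analysis defines the main outcome as the change in hamstring isometric peak force between weeks 4 and 12 and continues: "The main hypothesis will be tested by comparing the changes in the mean difference between the intervention group" and the standard-care group. The fallback is a Mann-Whitney test. A repeated-measures ANOVA of rehabilitation and time is planned for all measured variables. Hamstring flexibility (AKET) and IKDC, which Specific Objectives places pre-operatively and at 12 weeks, "will be summarised and evaluated in a manner consistent with the primary result". None of these analyses names a covariate.

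The Research Hypothesis concerns the level at week 12: patients given ULIT "will have better hamstring strength at 12 weeks post-operatively compared to participants receiving a standard care rehabilitation program alone".

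**The concern.** The pre-operative test is the only value of the primary measure that treatment cannot have affected, and the main comparison does not use it. The value that is used, week 4, is subtracted with its slope fixed at 1. So the measurement error of that test enters in full, whatever its true relation to week 12. IKDC and AKET do use their pre-operative value, but again with the slope fixed at 1.

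At stake are precision in a trial planned on 14 evaluable patients per arm, and protection against a chance difference in pre-operative strength. Simple randomisation does not guard against such a difference.

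**Working it through.** **Inputs from the protocol.** Two-sided 5% level ("p-value of less than 0.05 (two-tailed) for all conducted tests") and "type I error of 0.05, type II error of 0.2, 80% power" (Sample Size); 14 per group, raised to 16 for 10% attrition; involved-limb hamstring SDs of 0.5 at week 4 and 0.8 at week 12 (Table 1 under Sample Size).

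**Assumptions.** The protocol gives no correlations. I take 0.5 between weeks 4 and 12, and ρ = 0.3 or 0.5 between the pre-operative test and each later test. I read the unnamed between-arm test as a two-sample t-test on changes.

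**The plan's own figures.** 14/0.9 = 15.6, rounded up to 16, reproduces. The 14 itself cannot be reproduced, because no target difference is stated beside the "population standard deviation for the main outcome measure amount of 0.71". I therefore fix the difference at the value giving the unadjusted change comparison 80% power with 14 per arm: 1.10 SD by noncentral t.

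**Change score.** SD = √(0.5² + 0.8² − 2×0.5×0.5×0.8) = √0.49 = 0.70, so the difference is 1.10×0.70 = 0.77. With both SDs equal to 0.70 the change SD is also 0.70.

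**Residual SD of 12-week force.**
- Pre-operative force only: SD₁₂√(1−ρ²).
- Pre-operative and week-4 force: SD₁₂√(1−R²), with R² = (ρ² + 0.5² − 2×ρ×0.5×ρ)/(1−ρ²). This gives 0.25/0.91 = 0.275 at ρ = 0.3 and 0.25/0.75 = 0.333 at ρ = 0.5.

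Power is for 0.77 divided by the residual SD, less one degree of freedom per covariate. The lower figure in each range also multiplies the variance by 1 + 1/24 (one covariate) or 1 + 2/23 (two) for random covariate imbalance with 28 patients.

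| SDs, week 4 / week 12 | ρ | Planned change | Pre-operative only: residual SD, power | Both covariates: residual SD, power |
|---|---|---|---|---|
| 0.5 / 0.8 (table) | 0.3 | 80% | 0.763, 71–73% | 0.681, 79–82% |
| 0.5 / 0.8 (table) | 0.5 | 80% | 0.693, 79–81% | 0.653, 82–85% |
| 0.7 / 0.7 | 0.3 | 80% | 0.668, 82–83% | 0.596, 88–91% |
| 0.7 / 0.7 | 0.5 | 80% | 0.606, 89–90% | 0.572, 91–93% |

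**IKDC and AKET.** With equal SDs the change score has variance 2σ²(1−ρ) and ANCOVA has σ²(1−ρ²), a ratio of (1+ρ)/2. That is 0.65, 0.75 and 0.85 at ρ = 0.3, 0.5 and 0.7. An outcome with 80% power on the change score would have 92–93%, 89–90% and 84–86%.

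**Chance imbalance.** The difference in mean pre-operative strength has SD √(2/14) = 0.38 to √(2/16) = 0.35, in SD units. The probability that it exceeds 0.5 SD is 19% and 16% respectively. The effect on the planned contrast depends on the correlation of pre-operative force with the change, (0.8ρ − 0.5ρ)/0.70 at the table SDs: 0.13 at ρ = 0.3 and 0.21 at ρ = 0.5. With equal SDs it is zero. A 0.5 SD imbalance then shifts the contrast by at most 0.5×0.21 = 0.11 change SDs, about 10% of the 1.10 SD difference.

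**The case against.** An unadjusted randomised comparison is valid and unbiased, and covariate lists are often left to an analysis plan, which is not at hand. The first part stands. The second carries less weight, because the protocol does fix the comparison and its fallback, and both are unadjusted.

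A reader might infer that power would rise from 80% to about 90% on the primary outcome, or that about 0.18 SD of imbalance passes into the result. Both figures (ρ = 0.5) take an unadjusted comparison of 12-week force as the reference. The protocol plans no such comparison; it plans changes, which already remove week-4 imbalance and stable differences between patients. Nor do the documents support a strong correlation: the pre-operative test precedes tendon harvest, and the Background attributes early weakness largely to the donor site and to inhibition.

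It is also too strong to say that the pre-operative value is never used. IKDC and AKET are compared from pre-operative to 12 weeks. The repeated-measures ANOVA may include baseline strength, though as an outcome level rather than a covariate. With two time points its group-by-time test is the change-score test again.

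The week-4 test follows randomisation. ULIT is taught in the fourth week, and Data Collection allows ±14 days, so some week-4 tests may fall after training has begun. This applies to the present plan too, which subtracts week-4 force with slope 1. At the table SDs the ANCOVA slope would be (0.5−0.3×0.3)/(1−0.3²)×0.8/0.5 = 0.72 at ρ = 0.3, or (0.5−0.25)/(1−0.25)×0.8/0.5 = 0.53 at ρ = 0.5. Any early effect would be removed less, not more.

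**Conclusion.** The point holds in a moderate form. The plan probably loses precision; the documents do not show that it wastes power, and the planned comparison is not biased.

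For the primary outcome, adjusting for both earlier values is close to neutral at worst: about -1 to +5 points of power at the table SDs, and up to about +13 with equal SDs. It also corrects chance imbalance in pre-operative strength, whose effect on the planned contrast is modest. Adjusting for pre-operative force alone is not a safe replacement, since at the table SDs and ρ = 0.3 power falls to 71–73%.

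The gain is clearer for IKDC and AKET, with 15% to 35% less variance over ρ = 0.7 to 0.3. This assumes equal SDs before surgery and at 12 weeks.

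All of these sizes rest on assumed correlations and on the source study's SDs, which are torques in Nm/kg, whereas this trial analyses peak force.

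**What to change.** In Statistical Analysis:

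- Make the primary analysis an ANCOVA of 12-week operated-limb hamstring peak force on arm, with pre-operative and week-4 force as covariates for every patient. Using the 4-to-12-week change as the response with the same covariates gives the same arm estimate. Report the adjusted difference with its 95% CI and p-value.
- Apply the week-4 covariate to all patients, not according to when each was tested.
- Keep the unadjusted comparison of changes as a sensitivity analysis. Add a second one that leaves out week-4 force, because that test follows randomisation.
- Analyse 12-week IKDC and AKET by ANCOVA on their pre-operative values.

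The cost is a rewording before the data are analysed. No new visits, patients or software are needed, as SPSS fits these models. One or two error degrees of freedom are used, and power could fall very slightly if the correlations are weak. Missing pre-operative values should be rare, because baseline testing is a condition of randomisation. A missing week-4 value needs a stated rule, but the planned change score needs one too.

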### **Intervention Fidelity**

A physiotherapist will conduct follow-up phone calls to evaluate exercise adherence for both groups. They will use standardized guidelines and handouts to encourage patients' exercise adherence, minimizing biases. A flexible and patient-centred approach is applied to address a patient's deviation from their rehabilitation protocol. This involves assessing and reevaluating the patient's progress, modifying the rehab plan for individual needs, rescheduling missed sessions, maintaining weekly communication (online exercise diary), documenting changes and analysing data under an intention-to-treat (ITT) protocol to reduce bias and preserve randomisation.

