### **Withdrawal from Trial**

Following ACLR, each participant will have a scheduled follow-up visit at the HCTM Orthopaedic Outpatient Clinic. Every effort will be made to meet each participant's feasibility in attending the designated follow-up appointments (For example, flexible appointment times and dates). If they withdraw their consent, they will no longer be participants and will continue to receive the standard care rehabilitation and scheduled Orthopaedic Clinic follow-up. Information collected up to this point will be included.

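### Intention-to-treat is given as the handling of missing data, but the tests named use only patients with every required visit, so the analysis as written is complete-case under an ITT label

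*Protocol*

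**What the plan says.** On missing values, the Statistical Analysis section has two sentences. The first is "The missing data will be analysed according to the intention-to-treat concept", and it goes on to refer to the arms to which patients were allocated. The second is "Descriptive analysis, on the other hand, will describe missing data patterns in great detail to look for possible biases". No imputation, likelihood-based model or missing-data assumption is named.

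The same section fixes the tests. For the main outcome, "the mean changes in hamstring isometric peak force between 4 and 12 weeks, will be assessed using a paired t-test", followed by a comparison of that change between groups. If the distribution is unsuitable, "a non-parametric test (specifically, the Mann-Whitney test) will be conducted". For the longitudinal data, "A repeated measures analysis of variance (ANOVA) will be used to examine the impact of rehabilitation and time on all the measured variables". The software is SPSS.

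ITT is promised elsewhere too. Intervention Fidelity speaks of "analysing data under an intention-to-treat (ITT) protocol to reduce bias and preserve randomisation", and Blinding repeats the commitment. Withdrawal from Trial says of patients who withdraw consent: "Information collected up to this point will be included". Randomisation and Allocation places randomisation after the preoperative baseline. Sample Size allows for 10% attrition.

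**The concern.** ITT answers one question: who is analysed, and in which arm. It leaves open how an unobserved outcome is treated. Here it is offered as the answer to the second question, next to tests that settle it by omission. A week-4-to-12 change exists only for patients measured at both visits. Classical repeated-measures ANOVA drops any patient who lacks one of the visits in the model.

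Two things are at stake. First, if patients who stop attending recover differently, and participants know their group, the completer comparison can be biased while the report calls it ITT. Second, measurements already taken go unused in the tests that matter: a patient measured at weeks 4 and 8 who withdraws before week 12 enters neither the primary change nor an ANOVA over the three postoperative visits.

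**Working it through.** **Inputs from the protocol.** 14 evaluable per group, 10% attrition, 16 per group and 32 in all (Sample Size); strength visits preoperatively and at weeks 4, 8 and 12 (Abstract); preoperative baseline complete before randomisation (Study Design; Randomisation and Allocation).

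**The plan's own figure.** 14 / 0.90 = 15.6, rounded up to 16 per group, or 32. This reproduces. Applied to those randomised, 32 × 0.90 = 28.8 evaluable and 32 × 0.10 = 3.2 without a primary change score. So the primary comparison keeps about 14 per arm, as intended, but omits about 3 randomised patients.

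**What each test needs.**
- Week-4-to-12 change (t-test or Mann-Whitney): weeks 4 and 12.
- Repeated-measures ANOVA of postoperative strength: weeks 4, 8 and 12. Adding the preoperative value costs no patients, since everyone has it before randomisation.
- A patient lost between randomisation and week 4 can enter neither.
- A patient who misses only week 8 leaves the ANOVA but keeps the primary change.

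**Range for missed visits.** The protocol gives no rate per visit. Assume each postoperative visit is missed independently with probability m. Then 32(1−m)² keep the change and 32(1−m)³ have all three visits. For comparison, 32(1−m³) have at least one postoperative visit and so add an outcome to a model that uses every observed value.

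| m | Weeks 4 and 12 | Weeks 4, 8 and 12 | At least one |
|---|---|---|---|
| 5% | 28.9 | 27.4 | 32.0 |
| 10% | 25.9 | 23.3 | 32.0 |
| 15% | 23.1 | 19.7 | 31.9 |

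The last column is favourable because independent misses rarely coincide. Patients who drop out before week 4 would not be recovered.

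**Possible bias, as an illustration.** Take the involved-limb hamstring SDs in the table under Sample Size (0.5, 0.9 and 0.8 Nm/kg at weeks 4, 8 and 12), and assume normal values, a common correlation r between visits and no true treatment effect. Let all three expected losses fall in the ULIT arm, on the three patients weakest at week 8. Removing the lowest 3 of 16 normal values raises the mean of the other 13 by 0.311 SD. The completer contrast is then biased towards ULIT by 0.311 × r × (0.8 − 0.5):
- r = 0.3: 0.03 Nm/kg
- r = 0.6: 0.06 Nm/kg
- r = 0.8: 0.07 Nm/kg

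The tabulated mean gain from week 4 to week 12 is 1.55 − 1.0 = 0.55 Nm/kg, so this is roughly 5% to 14% of it. The missingness here depends on the observed week-8 value, which the completer tests ignore and a mixed model uses.

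**The case against.** The protocol nowhere mentions complete cases or listwise deletion; that follows from how the tests behave. A t-test or an ANOVA can be run after imputation, and the imputation method is commonly left to a statistical analysis plan, which may exist. The ITT sentence can be read simply as analysis by allocated arm. Missing-data patterns will be described, and Data Management and Confidentiality has unavailable data recorded on the case report form.

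Much of this stands. A reader might infer that the named tests make ITT impossible; they do not, if values are imputed. A reader might also infer that data from withdrawn patients are thrown away altogether. The withdrawal sentence does not promise each such patient a place in the primary test, and their values can still serve in descriptive summaries or in comparisons at weeks 4 and 8. Finally, a reader might take about 23 patients as the expected analysis set and conclude that the trial falls below 14 per arm. That count needs 10% independent loss at each visit and concerns only the three-visit ANOVA, for which the trial was not sized. On the same assumption 25.9 keep the primary change, and at the protocol's overall 10% the figure is 28.8. The IKDC and flexibility measures are compared only preoperatively and at week 12 (Specific Objectives), so the three-visit count does not apply to them.

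What does not fall away is the mismatch. The protocol itself states both the rule and the tests, and the rule does not supply what the tests lack. Describing missing-data patterns does not change who is analysed.

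**Conclusion.** The point holds in limited form. As written, the analysis of hamstring strength is complete-case and does not deliver the ITT analysis promised in three sections; partial data from withdrawn patients do not enter the named tests where a required visit is missing. At the planned attrition about 3 of 32 patients are left out of the primary comparison and about 28 to 29 remain, so the sizing is not undermined. The harm is a mislabelled analysis set and possible bias. In the adverse one-arm illustration that bias is about 0.03 to 0.07 Nm/kg; it would differ under other patterns of loss. There is some further loss in the ANOVA when week 8 is missed. The conclusion rests on standard behaviour of the tests and on no imputation being applied. The counts by missed-visit rate rest on an assumed rate and on independence. The change should be made before the data are analysed.

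**What to change.** Limit the ITT sentence to the analysis set: all randomised patients, in their allocated arm. State the handling of missing values separately.

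Replace the completer t-test and the between-group repeated-measures ANOVA for hamstring strength with one linear mixed model (SPSS MIXED, REML, unstructured covariance, small-sample degrees of freedom):
- **Outcomes:** operated-limb strength at weeks 4, 8 and 12.
- **Terms:** group, visit, group-by-visit, and the preoperative value as covariate.
- **Primary contrast:** the group difference in the week-4-to-12 change, as the Statistical Analysis section has it. Report the week-12 group difference alongside, since that is what the Research Hypothesis addresses.
- **Assumption:** missing at random given the observed values, stated explicitly.
- **Sensitivity analysis:** shift the missing week-12 values in the ULIT arm downward over a range fixed in advance.

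Do not enter week 4 as a covariate. It is measured after randomisation, its ±14-day window overlaps the start of ULIT in the fourth week, and patients without it would be dropped. If the Mann-Whitney test is kept, label it a completer analysis.

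The cost is analysis wording, with the same software and no new data. It is not purely cosmetic: the primary analysis becomes a model instead of a simple t-test, and patients with no postoperative visit still contribute no outcome.
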